### Statistical analysis method

#### Selection and completion

Cases were selected from among those who completed the study and those who dropped out. The selected cases and number of analytical datasets are described for safety and effectiveness. Cases not selected for PPS will also be listed.

#### Baseline equalization analysis descriptions

Baseline was defined as 0 days (when subjects were enrolled). The equilibrium analysis of basic values is focused on the basic demographic characteristics, vital signs, and indices related to curative effect to demonstrate whether the two groups of basic conditions are comparable. According to data distribution, the *t* test or Wilcoxon rank-sum test will be applied to compare the quantitative index of the two groups (such as ages, disease courses, blood glucose, glycohemoglobin [GHb]) by listing the number of cases, mean, SD, median, maximum, and minimum. The chi-square test and Fisher’s exact test are used to compare the qualitative index (such as gender, nationality, marital status, heart rate (HR), past history, family history, allergy history, previous treatment) by listing frequency and percentage.

#### Comparison of factors affecting test evaluation

For analysis of concurrent medication, the number and percentage of cases will be listed and compared using the chi-square test and Fisher’s exact probability method. For analysis of medication compliance, the number of noncompliant cases, those taking < 80% or > 120% of the stipulated dose, and compliant cases, those taking 80–120% of the stipulated dose, and the percentage of each are to be listed and compared using the chi-square test and Fisher’s exact probability method.

The medication period is the time of final medication minus the time of first medication plus 1 day. The number of cases, mean, SD, median, maximum, and minimum will be calculated and compared using the chi-square test and Fisher’s exact probability method.

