### Safety assessment and adverse events

Safety will be monitored for 6 months after the intervention and evaluated on the basis of the incidence of AEs, including clinically significant changes in physical examinations, vital signs, and standard clinical laboratory tests. Vital signs include body temperature, blood pressure, respiration, heart rate, and similar factors at months 0–6 Routine blood examination, routine urinalysis, and routine stool examination will be done at months 0, 3, and 6. ECG, five items assessing liver function (alanine aminotransferase, aspartate aminotransferase, γ-glutamyl transpeptidase, alkaline phosphatase, and total bilirubin), renal function (blood urea nitrogen), and SCr will be measured at months 0, 3, and 6. In addition, we will make at least one on-site monitoring visit during the study to ensure that each participating center complies with the study protocol and GCP principles. AEs, such as signs and symptoms and other ailments, will be documented at every study visit. Each AE will be classified as a mild, moderate, or severe AE, and its correlation with the intervention drugs will be assessed. Severe AEs will be reported to the principal investigator and the ethics committee within 24 h. The data and AEs will be accurately and appropriately recorded on the CRF. All of the AEs will be recorded, monitored, and treated until properly resolved. The schedule of enrollment, interventions, and assessments is presented in Fig. 3.

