### Statistical analysis

Three analysis sets will be used for analyzing data. First is the full analysis set (FAS), which refers to the ideal set of subjects as close as possible to the principle of intentionality analysis (including all of the subjects randomized to enroll and receive at least one treatment). If any given case is missing a main variable, the results of the closest observation are carried forward to the absence of the test data. The number of subjects evaluated at the end of each group is kept as consistent as possible before the start of the study. Second is the per-protocol set (PPS), in which all of the factors are in accordance with the research plan; patients show good compliance, using 80–120% of the prescribed dose; the CRF contains the details of the case; and the main variables can be determined. All of the baseline variables must be available, and there must be no major violation of the test plan. Third is the safety analysis set (SS), in which all of the subjects must receive at least one treatment after randomization.

Demographic and other baseline characteristics and efficacy analysis are set as the FAS and PPS. Safety analysis procedures are set as the SS. Data will be collected and analyzed using SAS 9.3 software (SAS Institute, Cary, NC, USA), and statistical analysis will be completed by the third-party personnel statisticians. All of the statistical tests are two-sided, and statistical significance is set at *P* ≤ 0.05.

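### The medication period, a number of days, is assigned chi-square and Fisher's exact tests with no categories, against the protocol's own rule for quantitative variables; the impact is modest

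*Protocol article*

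**What the plan says.** In the section on comparison of factors affecting test evaluation, the protocol article defines the variable: "The medication period is the time of final medication minus the time of first medication plus 1 day". The next sentence gives the summary and the test: "mean, SD, median, maximum, and minimum will be calculated and compared using the chi-square test", together with Fisher's exact method. No cut-points or duration classes are stated.

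The preceding paragraph of that section assigns the same two tests to concurrent medication and to compliance (below 80% or above 120% of the stipulated dose, versus 80–120%). Both are categorical, so the tests suit them.

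The baseline section sets the general rule. For quantitative variables, "the *t* test or Wilcoxon rank-sum test will be applied to compare the quantitative index of the two groups", depending on the distribution. Chi-square and Fisher's exact test are for the "qualitative index (such as gender, nationality, marital status, heart rate (HR), past history, family history, allergy history, previous treatment) by listing frequency and percentage". That second list includes heart rate, which the safety section treats as a measured quantity: "Vital signs include body temperature, blood pressure, respiration, heart rate, and similar factors at months 0–6".

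**The concern.** Neither chi-square nor Fisher's exact test compares means or medians. Applied to ungrouped days, either test treats each distinct duration as an unordered label, so 20 days and 170 days differ no more than 169 and 170. The named test therefore does not match the summary it is attached to, and it departs from the rule in the baseline section.

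The article plans for 20% dropout and carries the closest observation forward when a main variable is missing. A difference between arms in time on treatment is one of the things a reader would want to see before trusting carried-forward MDNS values. A non-significant P value from a test that can hardly reject would be falsely reassuring.

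**Working it through.** **Comparison within the article.** Number of cases, mean, SD, median, maximum and minimum is the article's standard summary for measured variables. The test paired with it is:

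| Section | Between-group test |
|---|---|
| Baseline, quantitative variables | t test or Wilcoxon rank-sum |
| Effectiveness analysis (MDNS) | t test or Wilcoxon rank-sum |
| Secondary index (NCV, symptoms) | t test or Wilcoxon rank-sum |
| Monitoring index (glucose, GHb, BP, lipids) | t test and Wilcoxon rank-sum |
| Medication period | chi-square and Fisher's exact |

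The medication period is the only exception.

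**Inputs for the size of the effect.** From the article: 188 patients at 1:1, so 188 / 2 = 94 per arm; 6 months of treatment; "All of the statistical tests are two-sided, and statistical significance is set at *P* ≤ 0.05". Not in the article, hence assumed: the distribution of days on medication and the difference between arms. The article states no figure on this point, so there is nothing to reproduce.

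**Method.** Simulated trials, 2,000 per scenario. Chi-square was run on the table of 2 arms by k distinct whole days, next to the t test and Wilcoxon test on the same data.

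*Early stopping.* Completers at 168 days with SD 3 or 7; early stoppers uniform over the course.

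| Stopping early | Chi-square | Wilcoxon | t test |
|---|---|---|---|
| 20% vs 20% (no difference) | 0.25% | 5% | 5% |
| 10% vs 30% | 1–2% | 63–66% | 84–85% |
| 10% vs 35% | 2% | 82–86% | 95% |

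The tables had about 48–66 distinct durations, and about 85–95% of expected counts were below 5. A separate simulation with completers at 180 days, SD 4, gave about 1% for chi-square and 68% for Wilcoxon at 10% versus 30%.

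*Normally distributed days.* SD 10, 20 and 30 days:

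| Difference | Chi-square | Wilcoxon | t test |
|---|---|---|---|
| 0 | 1.5%, 1%, 0.2% | 5–6% | 5–6% |
| 0.5 SD | 11%, 3%, 1% | 90–91% | 92–93% |
| 0.8 SD | 43%, 13%, 4% | about 100% | about 100% |

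*Exception.* With 20% stopping early in both arms, completers clustered at SD 3 and one arm shifted by 5 days, chi-square rejected in every run, as did Wilcoxon; the t test rejected in 13%. At SD 7 with the same shift the rates were 13%, 87% and 14%. So chi-square does not always miss a difference.

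**What the compliance comparison would show.** Take 10% versus 30% stopping uniformly over days 1–179, and assume that stopping before day 144 (0.8 × 180) counts as under 80% of the dose. The share of stoppers who are non-compliant is 143/179 ≈ 0.80, giving about 8% versus 24%. With 94 per arm:

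- pooled proportion 0.16; null SE = √(2 × 0.16 × 0.84 / 94) ≈ 0.0535
- alternative SE = √((0.08 × 0.92 + 0.24 × 0.76) / 94) ≈ 0.0522
- power ≈ Φ((0.16 − 1.96 × 0.0535) / 0.0522) = Φ(1.06) ≈ 0.85

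Simulation gives about 87% for chi-square and 83% for Fisher's exact test.

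**The case against.** The strongest reply is that little would be lost. In the very scenario where chi-square on days fails, the compliance comparison already planned in the same section picks up the imbalance in about 83–87% of trials, more often than Wilcoxon on days. The mean and median of the medication period are reported whatever the P value, and reasons for withdrawal are recorded. This stands, given the assumption linking early stopping to dose taken. A reader might infer that differential stopping would go unseen under this plan; the article does not support that.

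A second reply is that the simulated test, an asymptotic chi-square with one column per day, is only one reading of a sentence that also names Fisher's exact test. This stands in part. The very low rejection rate with equal arms belongs to the asymptotic version: a permutation version of the same table rejected in 5.1% of trials with equal arms. Its power at 10% versus 30% was still only about 11%, because it ignores order too. Fisher's test itself was not simulated on the day-level table.

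A third reply is that heart rate reported by frequency and percentage is coherent if it is classed, for example as normal or abnormal. That is fair. It is tempting to call this the same error, but the text shows at most an unstated category.

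Finally, the sentence looks like wording carried over from the compliance paragraph just before it. That is plausible, but it remains the stated plan.

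**Conclusion.** The point holds as an error in a stated analysis rule: a number of days is given a test for categories, with no categories defined, against the article's own rule for quantitative variables. This rests on the text alone and needs no assumption.

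The loss of power does depend on assumptions. Under the early-stopping scenarios it is large (about 1–2% against about 65% and 85%), but it is not universal, as the tightly clustered case shows.

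The practical impact is modest. The MDNS, NCV and symptom comparisons use suitable tests, per-protocol membership uses the 80–120% dose rule and not days, and the sample size is unaffected. The heart-rate listing is a secondary point of clarity.

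**What to change.** Replace the test named for the medication period with: *Medication period will be compared between groups with the t test or Wilcoxon rank-sum test, according to data distribution.* Keep chi-square/Fisher's exact test for compliance and concurrent medication. If a categorical comparison of duration was intended, state the classes.

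In the baseline section, either state the heart-rate categories or move heart rate to the quantitative list.

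The cost is one sentence plus one list entry, in the protocol or the statistical analysis plan. No new data or design change is needed; it should be settled before unblinding.

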#### Effectiveness analysis

For the main endpoint of curative effect, the MDNS and its changes relative to baseline after treatment are described. The number of cases, mean, SD, median, maximum, and minimum will be calculated and compared within each group using a paired *t* test or the Wilcoxon signed-rank test. Changes relative to baseline after treatment will be compared between groups using the *t* test or the Wilcoxon rank-sum test.

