**Methods/design:**

We are conducting a multicenter, placebo-controlled, double-blind, randomized, controlled clinical trial as a means of assessing the therapeutic effects of traditional Chinese medicine (TCM) treatment. A total of 188 patients will be randomized in a 1:1 ratio to a treatment group (TangBi Formula plus mecobalamin) and a control group (placebo plus mecobalamin). The test period lasts 6 months, during which all of the patients will be given standard medical care as recommended by established guidelines. The primary outcome will be development of differences in changes in clinical symptoms and signs in patients and changes in Michigan Diabetic Neuropathy Score (MDNS) between the two groups before and after treatment. The secondary outcome will be changes in nerve conduction velocity and in single clinical signs and symptoms. Safety assessments and adverse events will also be evaluated.

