### Design overview

The study design will integrate rigorous contemporary clinical research methodology in accordance with the principles set out in the Declaration of Helsinki and good clinical practice (GCP) guidelines according to the theory that guides the appropriate use of TCM in clinical practice. The rigorous design, organization, and conduct of the trial are supervised by a steering committee comprising two members from each participating center in addition to the chairman, scientific coordinator, and statistician. Six clinical centers in mainland China will participate in the trial, including Guang’anmen Hospital of the China Academy of Chinese Medical Sciences, the First Affiliated Hospital of Liaoning University of Traditional Chinese Medicine, the First Affiliated Hospital of Anhui University of Traditional Chinese Medicine, Hubei Hospital of Traditional Chinese Medicine, Zhengzhou City Hospital of Traditional Chinese Medicine, and Hebei Yiling Hospital. Data management and statistical analyses will be performed by independent data handlers and data analysts at the Institute of Basic Research in Clinical Medicine, China Academy of Chinese Medical Sciences. All of the patients must personally sign and date an informed consent document before randomization.

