### Intervention measures

All patients in the group will be treated with conventional treatment, which includes oral mecobalamin (500-mg tablet three times per day), diet, exercise, and oral medicine, to ensure access to steady levels of blood glucose, blood lipids, and blood pressure according to American Diabetes Association guidelines. On this basis, subjects will be randomly assigned to receive placebo (6 g/bag two times per day) or TangBi Formula (6 g/bag two times per day) by the central randomization system using a randomly permuted block design with block sizes of two and four. Upon production, study medications will be packaged and transferred to numbered bottles by designated pharmacists according to the randomized list prepared by the trial statistician. The treatment will last for 6 months. All of the people involved in the trial (patients, investigators, project manager, data management team, clinical research associates, and statisticians) will be masked with respect to the group assignments. Outcome analyses will be performed by analysts blinded to the group assignments by use of a central randomization system in which the codes will be kept by an independent allocator and revealed only after treatment and analyses are completed.

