### Sample size

According to the preliminary study of TangBi prescription data, the placebo group scale (MDNS) score difference was 3.45 and the TangBi prescription scale score was 4.14, with an SD of 1.33. The sample size was estimated using a hypothesis test formula of measurement data: *N* = 2 × [(Zα + Zβ) × δ/*d*]^2^, where *N* is the sample size and δ is the estimated SD, *d* is two groups’ continuous variable mean difference, and Zα and Zβ are the corresponding standard normal differences. Supposing α = 0.05 and β = 0.10, according to the one-sided check table, the quantile Zα = 1.64485 and Zβ = 0.84162, and these are entered into the formula. It is estimated that a sample size of 78 subjects per group will be required, taking into account 20% dropout and withdrawal. This results in 188 participants in total. Intention-to-treat analysis will be used to minimize bias due to dropouts.

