### Outcome measurements

#### Primary outcome measures

Changes in clinical signs and symptoms in patients with DSPN: Changes in clinical signs and symptoms will be evaluated prior to treatment and at weeks 12 and 24 of the treatment phase.Changes in the MDNS are compared between the two groups before and after medication. The clinical signs and symptoms of patients will be recorded using the MDNS. MDNS will be evaluated prior to treatment and at weeks 12 and 24 of the treatment period.

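### The primary MDNS comparison is left open between an unadjusted t test and a Wilcoxon test with no rule for choosing; one baseline-adjusted ANCOVA would fix the estimate and gain precision at no cost

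*Protocol article*

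**What the plan says.** The Effectiveness analysis section sets the between-group method for the primary endpoint, the change in MDNS: "Changes relative to baseline after treatment will be compared between groups using the *t* test or the Wilcoxon rank-sum test". No covariate or centre term is attached to this comparison, there or elsewhere in the article. The section on the secondary index of curative effect repeats the method for NCV and symptoms.

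The information needed for adjustment will be collected. On the score: "MDNS will be evaluated prior to treatment and at weeks 12 and 24 of the treatment period". On sites: "Six clinical centers in mainland China will participate in the trial". Allocation is made "by the central randomization system using a randomly permuted block design with block sizes of two and four"; stratification by centre is not stated.

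A criterion for choosing between the two tests appears once, in the section on baseline comparisons: "According to data distribution, the *t* test or Wilcoxon rank-sum test will be applied to compare the quantitative index of the two groups". The Effectiveness analysis section contains no such criterion.

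The Sample size section works with means: "the placebo group scale (MDNS) score difference was 3.45 and the TangBi prescription scale score was 4.14, with an SD of 1.33".

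**The concern.** Two things are at stake.

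The first is what the trial estimates. A t test addresses a difference in mean change, whereas a rank-sum test addresses a shift in ranks. Joined by a bare *or*, they leave the primary estimate unspecified. The trial is sized on a mean difference, so the analysis should commit to estimating one.

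The second is precision. Subtracting baseline is the same as fitting it with a slope of 1. Unless baseline and week-24 MDNS are almost perfectly correlated, the fitted slope is lower and the change score stays correlated with baseline. Chance baseline imbalance then adds noise to the treatment estimate, and variance that baseline could explain stays in the error term. ANCOVA removes it for the price of a degree of freedom.

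The article itself states the primary method, so this is not a detail left to a statistical analysis plan that is not shown.

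**Working it through.** **Inputs from the protocol article**
- Difference in mean change: 4.14 − 3.45 = 0.69; SD 1.33, read as the SD of change (Sample size).
- 78 per group, 20% dropout, 188 in total (Sample size); "A total of 188 patients will be randomized in a 1:1 ratio" (abstract), so 94 per arm.
- Tests two-sided at 0.05 (Statistical analysis).

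**Input not in the documents**
- r, the correlation of baseline MDNS with change. Assumed range in absolute value: 0.3 to 0.5.

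**Step 1. Reproduce the plan's figure.** N per group = 2 × [(Zα + Zβ) × SD / d]².
- Two-sided 5%, 90% power: 2 × [(1.95996 + 1.28155) × 1.33 / 0.69]² = 78.08, which matches the stated 78.
- Printed quantiles: 2 × [(1.64485 + 0.84162) × 1.33 / 0.69]² = 45.9, which does not match.
- 78 × 1.2 = 93.6, rounded to 94 per arm, and 2 × 94 = 188.

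The planned number therefore fits an unadjusted two-sided comparison of means. The text around it reads "Supposing α = 0.05 and β = 0.10, according to the one-sided check table"; the mismatch with the printed quantiles is a separate matter.

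**Step 2. How many patients are analysed.** If last values are carried forward in the full analysis set, as the withdrawal and Statistical analysis sections provide, about 94 per arm are analysed. If the 20% who drop out are lost, 94 × 0.8 = 75.2, about 75 per arm.

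**Step 3. Effect of adjusting for baseline.** Residual SD = 1.33 × √(1 − r²). Power is from the noncentral t, two-sided 5%, difference 0.69.

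| abs. r | Residual SD | Power, 94 per arm | Power, 75 per arm | Sample-size equivalent 1/(1 − r²) |
|---|---|---|---|---|
| 0 (no gain) | 1.330 | 94.3% | 88.4% | 1.00 |
| 0.3 | 1.269 | 96.0% | 91.1% | 1.10 |
| 0.4 | 1.219 | 97.1% | 93.1% | 1.19 |
| 0.5 | 1.152 | 98.3% | 95.4% | 1.33 |

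**Step 4. What the assumed r implies.** With equal variances at baseline and week 24, r² = (1 − ρ)/2, where ρ is the baseline-to-week-24 correlation. So ρ = 1 − 2r²: r = 0.3 gives ρ = 0.82, r = 0.4 gives 0.68 and r = 0.5 gives 0.50. As ρ approaches 1, r approaches 0 and the gain disappears.

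**Step 5. Centre.** Adjustment multiplies the residual variance by (1 − ICC), and the ICC is not given. For an assumed ICC of 0.05, at 78 per group and by the normal approximation, power goes from 96.3% to 97.0% at ρ = 0.5, from 94.0% to 95.0% at ρ = 0.7, and from 91.4% to 92.7% at ρ = 0.9. That is about one percentage point.

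**Step 6. Validity.** In simulations with normal data, six centres, ICC 0.05, 78 per group and 3,000 runs per setting, type I error was 4.3% to 5.9% across the t test, the Wilcoxon test and ANCOVA with centre. A blinded choice between t test and Wilcoxon by a Shapiro-Wilk test on pooled data (94 per arm, 6,000 null runs per distribution) gave 5.1% for normal, 4.7% for lognormal and 5.0% for rounded scores.

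**The case against.** The best defence is that nothing here is invalid. Under randomization an unadjusted comparison of change is unbiased on average, and chance imbalance adds variance, not systematic error. The sample size was derived for this comparison. With carry-forward the unadjusted test has 94.3% power, above the planned 90%. That stands, and it limits the point to an improvement.

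Five stronger readings are tempting, and the documents do not support them.

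- *Baseline MDNS is thrown away.* It is not. The change score uses it with a slope of 1, and only the gap between that slope and the fitted one is lost.
- *The primary test will be picked by the data distribution.* That criterion is written only for baseline comparisons. For the primary endpoint there is no rule at all.
- *The choice waits for unblinding.* The Intervention measures section keeps analysts blinded and releases the codes only once analyses are finished.
- *The open choice distorts the error rate.* The simulations show no distortion. They cover only one plausible selection rule, because the protocol gives none.
- *Centre must be in the model as a stratification factor.* Stratification by centre is not stated, so that argument is unavailable.

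Blinding limits opportunistic selection but does not say which quantity is estimated. Adequate power is not a reason to leave free precision unused, particularly if fewer than 94 per arm are analysed.

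**Conclusion.** The point holds as a weakness of pre-specification and efficiency. The missing choice between the t test and the Wilcoxon test is plain from the text and needs no assumption.

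The precision gain is certain in direction, apart from the few degrees of freedom spent, but uncertain in size. For r of 0.3 to 0.5 it is about 2 to 4 percentage points of power at 94 per arm and about 3 to 7 points at 75 per arm. At 75 per arm the unadjusted test falls slightly short of 90% and ANCOVA passes it throughout the range. These figures rest on the assumed r, on 1.33 being the SD of change, and on a two-sided 5% test. Baseline adjustment and a single named test carry the case; centre is expected to add little.

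**What to change.** Replace the two-test wording in the Effectiveness analysis section with one primary analysis: ANCOVA of week-24 MDNS (or its change from baseline) on treatment, with baseline MDNS as covariate and centre as a factor. Report the adjusted mean difference with its 95% CI. Keep the rank-based test as a named sensitivity analysis instead of an alternative. Use the same form for NCV in the section on the secondary index of curative effect, with the baseline value of each nerve as covariate.

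The cost is wording only. No new data, visits or patients are needed. When the article was submitted, 73 patients had been recruited and none had completed treatment, so at that point the change could be made before any week-24 result existed.
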